### **Hypotheses:**

1. The MORACS program will improve identification of STEMI
2. The MORACS program will improve 30-day mortality, 12-month mortality, time to reperfusion, length of hospital stay and readmission rates in patients with suspected ACS presenting to rural hospitals

Our proposal addresses a variation in clinical care that is deadly, costly, potentially preventable. Hub-and-spoke models have been shown to be effective in other clinical situations, but our application is a novel use of this approach. Our telehealth solution to this clinical issue will maximise the clinical support to many rural hospitals.

The NSW State Cardiac Reperfusion Strategy (SCRS) aims to deliver increased access to medical advice and reperfusion therapies in a timely manner for patients diagnosed with STEMI. Our approach is complementary to the SCRS and will in no way overlap with this. We aim to assist clinicians earlier in the diagnostic work-up, to prevent the diagnosis being missed. If a diagnosis of STEMI is made, the patient will be treated via the usual SCRS process.

Research design and methods (maximum 4 pages)

**Study design:** A prospective, cluster randomised controlled trial (RCT) to evaluate the effectiveness of a hub and spoke ACS management system to improve health outcomes for rural residents.

**Setting:** Hunter New England Local Health District in regional/rural NSW Australia. The following hospitals will be included:

Armidale, Barraba, Bingara, Cessnock, Denman, Dungog, Glenn Innes, Gloucester, Gunnedah, Guyra, Kurri Kurri, Merriwa, Moree, Murrurundi, Muswellbrook, Narrabri, Nelson Bay, Singleton, Scone, Tenterfield, Vegetable Creek, Walcha and Wialda;

These hospitals were selected because General Practitioners (GPs) or Career Medical Officers (CMOs) manage cardiology admissions, i.e. there are no Emergency Medicine specialists at these hospitals. Together they assess over 6000 chest pain presentations per year. The rationale for including GP and CMO staffed hospitals was that these were the hospitals with higher numbers of missed myocardial infarctions in our prior study (4).

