**Participants:** All patients presenting with chest pain for investigation to hospitals from rural and remote communities throughout the HNELHD. Notably, patients with prehospital ECGs performed by ambulance paramedics showing STEMI will NOT go through this process, they will go via existing SCRS pathways. All patients presenting to Emergency Departments, whether by self-transport or via ambulance without a prior STEMI diagnosis, will be included.

**Eligibility:** Inclusion criteria – Hospitals where GPs or Career Medical Officers (CMOs) manage ACS presentations will be included. All consecutive patients presenting to hospital with suspected ACS (eg. chest pain for investigation or other heart related symptoms such as shortness of breath or who are triaged as possible ACS) will be included.

Exclusion criteria – Hospitals staffed by Emergency Medicine specialists (FACEMs) will not be included. Our data suggest the rate of missed STEMI in these hospitals is low. There will be no patient-level exclusion criteria.

**Randomisation:** Hospitals will be randomised to receive the intervention (MORACS) or control (usual care). Randomisation will be undertaken independently by personnel from the HMRI statistical support unit. Randomisation will be stratified based on hospital size and medical staffing. Rural hospitals included in the study have bed numbers that range from 0 to 100. In most rural hospitals admissions are managed by on-call GPs where the GP attends as required. In a small number of rural hospitals admissions are managed by CMOs who are staffed 24 hours per day, therefore potentially able to offer more timely treatment. GP vs CMO staffing will be separately stratified to better identify different outcomes of care driven by differing medical management system in place.

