#### **Statistical methods and analysis:**

- 1) Power calculation: Based on local data, anticipated number of presentations to hospital with suspected ACS over a 12-month period are approximately 6,300. Of these an estimated 50% will require admission and investigation for ACS. Around 15% of the total patient group will have non-STEMI and a further 5% have STEMI, i.e. ~315 STEMI per year across all centres. An estimated 36% of the patients with STEMI will be missed and we wish to detect an absolute reduction in missed STEMI of 16%, i.e. 36% down to 20%, which will require 280 participants (140 per arm), at 80% power and  $p=0.05$ . We also include a design effect of 1.24 (assuming cluster sizes of 13 and  $ICC=0.015$ ) for a total of 338 patients across 26 clusters total. Therefore, it will take approximately 15 months to recruit. In the two-year timeframe, we will be able to analyse the rate of STEMI detection (primary endpoint) and will have a *median* 12-month follow-up for the secondary endpoints.
- 2) Evaluation of Results: Analysis of the primary outcome (the proportion of correctly identified STEMI) will be via logistic regression with adjustment for stratifying variables (size and staffing of hospital), and analysis of the secondary outcomes will be via linear and logistic regression.
- 3) Economic evaluation: Assuming an improvement in STEMI identification, three economic evaluations will be conducted. 1) From a health provider perspective, a cost-effectiveness analysis to report the resources required per unit improvement in the identification of STEMI. Costs will include the cost of the intervention as well as related costs such as hospital stay,

treatments and readmissions. The measure of effect will be based on the primary outcome (identification of STEMI). 2) A cost-consequence analysis will report the cost of the intervention and its range of consequences such as the change in STEMI identification, reperfusion times, hospital admissions, readmissions and MIs. 3) A modelling exercise to estimate costs and potential downstream impacts from the intervention over a ten-year time frame, these will include avoided healthcare costs as a consequence of improved STEMI detection and treatment, as well as adherence to secondary prevention therapies. This will be informed by data linkage with MBS and PBS.

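### The analysis sentence names no method for the randomised hospital, although the sample size assumes within-hospital correlation; as written, tests exceed 5%

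*Protocol*

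**What the plan says.** The Study design paragraph describes "A prospective, cluster randomised controlled trial (RCT"), and the Randomisation paragraph confirms the unit: "Hospitals will be randomised to receive the intervention (MORACS) or control (usual care"). Randomisation is stratified by hospital size and by GP or CMO staffing.

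Item 1 of Statistical methods and analysis allows for this design: "We also include a design effect of 1.24 (assuming cluster sizes of 13 and" an ICC of 0.015), "for a total of 338 patients across 26 clusters total".

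Item 2 of the same section sets the analysis. For the primary outcome, the proportion of STEMI correctly identified, it "will be via logistic regression with adjustment for stratifying variables (size and staffing of hospital"). For the rest, "analysis of the secondary outcomes will be via linear and logistic regression". The protocol nowhere mentions a hospital random effect, GEE, cluster-robust standard errors or an analysis of hospital summaries.

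**The concern.** Items 1 and 2 do not agree. Item 1 treats patients in the same hospital as correlated. Item 2 names models which, taken at face value, treat patients as independent given two hospital characteristics. Size and staffing are fixed covariates shared by several hospitals. They may absorb some of the between-hospital variance, but hospitals in the same stratum still differ, and that remaining variance falls on the treatment comparison because treatment is assigned by hospital.

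If the sentence is followed literally, standard errors are too small, intervals too narrow, and the primary test does not hold its stated 0.05. The problem grows with the number of patients per hospital, so it could be larger for mortality, MACE, readmission and length of stay. Hypothesis 2 places its mortality, length-of-stay and readmission outcomes in all patients with suspected ACS.

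**Working it through.** **Inputs from the protocol.** Missed STEMI 36% versus 20%, p = 0.05 (taken as two-sided), 80% power, 280 patients, cluster size 13, ICC 0.015, design effect 1.24, 338 STEMI in 26 clusters; about 6,300 suspected-ACS presentations and 315 STEMI per year; about 15 months of recruitment. The Setting paragraph lists 23 hospitals by name, so both 23 and 26 are used below.

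**The plan's own figures.**
- The usual two-proportion formula for 36% versus 20% gives 123 per arm (246 in total), or 135 per arm with a continuity correction. The stated 140 per arm gives 85% power.
- The design effect from the stated inputs is 1 + (13 − 1) × 0.015 = 1.18, not 1.24. A value of 1.24 needs ICC 0.02 with 13 per cluster, or about 17 per cluster at ICC 0.015.
- 26 × 13 = 338, which lies between 280 × 1.18 = 330 and 280 × 1.24 = 347.

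These discrepancies are a separate matter. Both design effects are carried forward.

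**Formula.** With m patients per hospital, DE = 1 + (m − 1) × ICC. A test that ignores clustering understates the standard error by a factor √DE, so its true two-sided type I error is 2 × [1 − Φ(1.96/√DE)].

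**Primary outcome, ICC 0.015.**
- m = 13: DE 1.18, √DE 1.09, 1.96/1.086 = 1.80, type I error 7.1%.
- m = 17.1 (315 × 1.25 = 394 STEMI over 23 hospitals): DE 1.24, √DE 1.11, 1.96/1.114 = 1.76, type I error 7.9%.

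A beta-binomial simulation (40,000 trials, 26 equal clusters of 13, unadjusted logistic Wald test) gave 7.1% at ICC 0.015 and 8.0% at ICC 0.02. Time to reperfusion is restricted to STEMI, so its clusters are the same size and the effect is similar if its ICC is similar.

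**Outcomes in all suspected-ACS patients.** 6,300 × 1.25 = 7,875 patients, which is 303 per hospital over 26 or 342 over 23. The protocol gives no ICC for these outcomes, so the ICCs below are assumptions. The highest is the value the protocol uses for STEMI identification.

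| Assumed ICC | DE (303 to 342 per hospital) | √DE | Type I error |
|---|---|---|---|
| 0.001 | 1.30 to 1.34 | 1.14 to 1.16 | about 9% |
| 0.005 | 2.51 to 2.71 | 1.58 to 1.65 | 22–23% |
| 0.015 | 5.53 to 6.12 | 2.35 to 2.47 | 40–43% |

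Simulation with 303 per cluster and a 10% event rate gave 8.7%, 21.4% and 40.6%. These figures assume equal hospitals and no variance absorbed by covariates. Unequal sizes would raise them and covariates may lower them.

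**Primary power once clustering is respected, 338 STEMI.**
- 26 equal hospitals, t critical value on 24 degrees of freedom: about 83% at DE 1.18 and 81% at DE 1.24.
- 23 equal hospitals: m = 338/23 = 14.7, DE 1.21, about 82% on 19 to 21 degrees of freedom.
- 23 hospitals with an assumed coefficient of variation of size of 0.8: DE = 1 + (1.64 × 14.7 − 1) × 0.015 = 1.35, so 338/1.35/2 ≈ 125 effective patients per arm. The standard error is √[(0.36 × 0.64 + 0.20 × 0.80)/125] ≈ 0.056, and power is about 78%.

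**The case against.** The strongest reply is that item 2 is a single sentence naming a family of regression. Mixed models and GEE are also forms of logistic and linear regression, item 1 shows that the authors had clustering in mind, and a statistical analysis plan, not available here, may supply the method. Part of this stands. A reader might infer that the investigators decided to ignore clustering; the protocol does not say so. The choice of small-sample correction and degrees of freedom is normal analysis-plan content, and its absence is not a fault. But the protocol does more than stay silent. It names a model and lists its covariates, two of them hospital-level, and leaves out the hospital itself. An analysis plan that added it would have to go beyond that wording.

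The second reply concerns size. The excess for the primary outcome is modest. For the secondary outcomes, a reader might infer that false-positive results would arise close to half the time. The protocol does not support that as a general statement. The ICC of 0.015 belongs to STEMI identification, the effect is mild at ICC 0.001, and time to reperfusion does not have the large clusters. The Outcomes section also sets no denominator for most secondary outcomes; the all-patient reading comes from Hypothesis 2. These limits affect the size of the problem and leave its direction unchanged.

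**Conclusion.** The point holds as an inconsistency within the protocol: the sample size assumes within-hospital correlation, and the analysis sentence provides no means of handling it. Followed literally, the primary test runs at about 7–8%, not 5%, on the protocol's own ICC and 13 to 17 STEMI per hospital. For outcomes in all suspected-ACS patients the excess lies anywhere from about 9% to 40–43% over assumed ICCs of 0.001 to 0.015. That range rests on 15 months of recruitment, equal hospitals and no variance absorbed by size and staffing. The upper end is conditional on borrowing the primary outcome's ICC and should not be reported as the expected error. Because the primary confirmatory test is affected and the remedy is a change of wording, it should be corrected before analysis.

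**What to change.** Replace the analysis sentence in item 2 with one that treats hospital as the cluster for the primary outcome and for every secondary outcome. Three forms are acceptable: a mixed model (logistic or linear) with a random hospital intercept, GEE clustered on hospital with a small-sample-corrected variance, or a cluster-level analysis of hospital summaries. Each should adjust for the stratification factors and use degrees of freedom based on the number of hospitals. One form should be chosen in advance.

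No further data collection is needed. The cost is wider intervals, which is their correct width. Primary power stays at about 81–83% with 338 STEMI if hospitals contribute equally. It falls to about 78%, just under the planned 80%, if the coefficient of variation of hospital size is 0.8. The protocol gives no such coefficient, so expected STEMI counts per hospital should be tabulated from local data to see which figure applies.

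### Adjustment for the randomisation strata is named for the primary outcome only; it should cover the secondary models too, within an analysis that respects clustering

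*Protocol*

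**What the plan says.** The Evaluation of Results item (Protocol, Statistical methods and analysis) describes both sets of models in one sentence. The primary analysis "will be via logistic regression with adjustment for stratifying variables (size and staffing of hospital"). For the rest, "analysis of the secondary outcomes will be via linear and logistic regression". The second clause names no covariates, and neither clause names a term for clustering by hospital.

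The Randomisation paragraph makes the hospital the unit of allocation and states: "Randomisation will be stratified based on hospital size and medical staffing". On staffing it adds: "GP vs CMO staffing will be separately stratified to better identify different outcomes of care driven by differing medical management system in place".

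Hypothesis 2 covers 30-day and 12-month mortality, time to reperfusion, length of stay and readmission in patients with suspected ACS. It is therefore tested wholly by the secondary models.

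**The concern.** The sentence attaches the adjustment to one outcome, and someone implementing it as it stands could fit the secondary models without the strata. That sits badly with the design. Stratifying makes the arms alike on size and staffing, so the true variance of the arm comparison is already lower. An analysis that leaves the strata out does not credit that reduction: between-stratum differences stay in the error term, the standard error is overstated and the test is conservative.

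The protocol itself expects staffing to affect care, and it notes that hospitals with round-the-clock CMO cover may treat sooner. The point has most force where hospitals contribute many patients each, because hospital-to-hospital variation then makes up much of the error and hospital-level factors can explain part of it. At stake is the ability to see an effect on clinical outcomes under Hypothesis 2.

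**Working it through.** **The plan's own figures.** No sample size, power or ICC is given for any secondary outcome, so there is nothing to reproduce directly. The nearest figure is the "design effect of 1.24 (assuming cluster sizes of 13 and" an ICC of 0.015) used for the primary outcome. Those inputs give 1 + 12 x 0.015 = 1.18; 1.24 would need an ICC of 0.02. That is a separate matter and does not drive what follows.

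**Inputs from the protocol.** About 6,300 presentations a year and 15 months of recruitment: 6,300 x 15/12 = 7,875. The Setting paragraph lists 23 hospitals, so m = 7,875/23 = 342 per hospital. The power calculation uses 26 clusters, which gives m = 303. For STEMI-only outcomes m = 13.

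**Assumptions.** An ICC of 0.001 to 0.015 for secondary outcomes (0.015 is the plan's value for missed STEMI); a share R2 of 0, 25% or 50% of between-hospital variance explained by the strata; hospitals of equal size; three strata of 9, 9 and 5 hospitals in the simulation.

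**Formula, analysis at hospital level.** Ratio of error variance with the strata to error variance without them:

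[ICC(1 - R2) + (1 - ICC)/m] / [ICC + (1 - ICC)/m]

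The relative width of the unadjusted interval is 1/sqrt(ratio).

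Worked case, ICC 0.015, m = 342, R2 = 25%: (1 - 0.015)/342 = 0.00288; (0.01125 + 0.00288)/(0.015 + 0.00288) = 0.790; 1/sqrt(0.790) = 1.125.

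| Outcome set | ICC | R2 | Variance ratio | Unadjusted interval wider by |
|---|---|---|---|---|
| All presenters, m = 342 | 0.015 | 25% | 0.790 | 12% |
| | 0.015 | 50% | 0.581 | 31% |
| | 0.005 | 25% | 0.842 | 9% |
| | 0.005 | 50% | 0.684 | 21% |
| | 0.001 | 25% | 0.936 | 3% |
| | 0.001 | 50% | 0.872 | 7% |
| STEMI only, m = 13 | 0.015 | 25% | 0.959 | 2% |
| | 0.015 | 50% | 0.917 | 4% |

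With m = 303 (26 clusters) and ICC 0.015 the ratios are 0.795 and 0.589, so the count of 23 or 26 makes little difference.

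**Simulation of hospital means** (23 hospitals, stratified allocation, ICC 0.015, m = 342, with and without strata terms):

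- Type I error without the strata is about 3.0% at R2 = 25% and 1.3-1.6% at R2 = 50%, against about 5% with them. Intervals are 12% and 32% wider.
- For an effect that gives about 79% power when the strata explain nothing, power without and with the strata is 82% v 88% at R2 = 25%, and 84% v 96% at R2 = 50%. At ICC 0.005 it is 81% v 85% and 83% v 92%.
- At R2 = 0, adjusting costs about 1 point of power or less.

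**The plan read literally, with no cluster term.** With 26 clusters of 303 and ICC 0.015 the design effect is 1 + 301.9 x 0.015 = 5.53. The correct interval is then sqrt(5.53) = 2.35 times the width the model reports, and type I error is about 40%. In simulation with stratum effects of 0.2 to 0.5 SD, the linear model's standard error was 0.0227-0.0237 without the strata and 0.0225 with them, against a true value of about 0.052. Type I error stayed at 38-41% either way in the linear model, and at 31-33% in a logistic model with a 20% event rate.

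**The case against.** The strongest reply is that the protocol is silent, not contradictory. It gives no covariate list for the secondary models, and such a list is commonly left to a SAP, which is not shown. That stands in part: a reader might infer that the strata have been deliberately dropped, and the text does not support this. What remains is that the authors dealt with covariates in this very sentence and named them for one outcome only.

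A second reply is that intervals from the plan as written would be too narrow, not too wide. This is correct. A reader might infer that the secondary intervals will be too wide under the stated plan; the document names no cluster term, so that reading fails. Needless width arises only once clustering is handled. It does still arise then: a hospital random effect or cluster-robust variance without the strata would leave the between-stratum variation in the error.

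A third reply is that the size rests on assumptions. It does. The document gives neither a secondary ICC nor an R2. Beds range from 0 to 100, so equal clusters are a simplification. Only a small number of hospitals have CMOs, which limits what staffing can explain. Nor do all secondary outcomes use every presenter: time to reperfusion is STEMI-only, and about half of presenters are expected to be admitted, which bears on length of stay. Finally, hospital-level calculations fit linear analyses best; the gain in patient-level logistic models may differ.

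**Conclusion.** The point holds as a conditional one about efficiency. The protocol names stratum adjustment for the primary outcome and not for the secondary outcomes, although the randomisation is stratified on both factors. In a cluster-aware analysis, omitting the strata would make all-presenter intervals about 9-12% wider (R2 25%) or 21-32% wider (R2 50%) at an ICC of 0.005 to 0.015, and would hold true type I error below the nominal 5%. For STEMI-only outcomes, or at an ICC near 0.001, the effect is at most a few per cent, and it vanishes if the strata explain nothing. There is no added false-positive risk from this omission, and no bias in the linear comparison of arms.

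It ranks below the missing cluster term in the same sentence, which acts in the opposite direction and is much larger. The two corrections are distinct: strata terms do not repair intervals that ignore clustering, and a cluster term does not supply the strata.

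**What to change.** Reword the Evaluation of Results item so that the primary and every secondary analysis adjusts for hospital size and hospital staffing, and so that this is done within the cluster-aware model chosen for each outcome (a mixed model or GEE with a small-sample correction, or an analysis of hospital summaries). Settle both parts before outcome data by arm are seen, so that whether to adjust is not open to choice later.

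The strata part costs one sentence. Both factors are known for every hospital at randomisation, so no data collection is added. The price is about two hospital-level degrees of freedom (with three strata, 21 falls to 19), worth about 1 point of power or less if the strata turn out to explain nothing.

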| Project summary     | 
One third of patients presenting to Australian hospitals with ST-segment-Elevation Myocardial Infarction (STEMI) do not receive primary reperfusion treatment, which is the standard of care (1, 2). In rural and regional Australia, primary reperfusion treatment involves thrombolysis which, if delivered in timely fashion, provides outcomes similar to primary percutaneous coronary intervention (PCI) (3). Failure to provide reperfusion doubles mortality, increases length of stay and increases readmission rates (2). A high level of clinical variation, due to misdiagnosis or treatment of acute coronary syndromes (ACS), has been found in NSW. Our research in Hunter New England Health Local Health District (HNELHD) shows that missed acute myocardial infarction (MI) from failure to correctly interpret electrocardiogram (ECG) and serum markers, is common leads to increased mortality and morbidity, and is overrepresented in rural hospitals that are maintained by GPs (4).
 
This proposal will randomize small rural hospitals to either usual care or a mandated transmission of ECG and troponin from spoke (rural) hospitals to a central hub service. Protocol directed advice will be given to the randomized rural hospital clinicians, and will channel patients into the existing ACS management structures: The State Cardiac Reperfusion Strategy (SCRS) for STEMI patients, and the NSW Chest Pain Pathway for non-STEMI patients. The primary outcome will be the difference in identification of STEMI in patients who present to rural hospitals.
 
A cost-effectiveness evaluation will report the resources required to increase STEMI identification. Secondary outcomes include major adverse cardiac events (MACE) and outcomes in non-STEMI. HNELHD has a proven track record in innovation in rural cardiology. If successful and cost-effective, this project will define a new paradigm for assessment and management of ACS in rural settings,
 |

|                                                       |                                                                                                                                                                                                                                                                                                                            |

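### All three economic evaluations are conditional on an undefined improvement in STEMI identification, which selects on the denominator of the cost ratio and leaves no planned evaluation after a null result

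*Protocol*

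**What the plan says.** Item 3 (Economic evaluation) under Statistical methods and analysis begins "Assuming an improvement in STEMI identification, three economic evaluations will be conducted". The three evaluations are:

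1. From the provider's viewpoint, "a cost-effectiveness analysis to report the resources required per unit improvement in the identification of STEMI". The effect in this ratio is the trial's own primary endpoint.
2. Costs set beside outcomes: "A cost-consequence analysis will report the cost of the intervention and its range of consequences". The consequences listed include the change in STEMI identification, reperfusion times, admissions, readmissions and MIs.
3. A ten-year model of costs and downstream effects that follow from better detection and treatment.

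The opening clause governs all three. No size or significance threshold is attached to the word improvement, and no economic analysis is described for a null or adverse result.

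The Project summary says "A cost-effectiveness evaluation will report the resources required to increase STEMI identification", with no explicit condition. The Follow-up, Outcomes and Measures paragraphs plan the record linkage, including MBS and PBS, without any condition on the primary result. Expected impacts of research says that the economic evaluations will feed a business case for wider adoption in NSW.

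**The concern.** There are two separate problems.

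**Selection on the denominator.** The estimate that decides whether the ratio is reported is also the estimate the ratio divides by. Trials in which chance made the effect look large pass the condition more often than trials in which it made the effect look small. Among reported results the effect is therefore too large on average, and the cost per extra STEMI identified too low. Because improvement is undefined, the strength of this selection is left open and could be settled after the result is known.

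**No planned answer after a null result.** A cost-consequence table sets costs beside outcomes and needs no favourable effect. The intervention also covers patients with non-STEMI, whom the power calculation puts at about 15% of presentations against 5% with STEMI. Stay, readmissions and resource use could change without a gain in STEMI identification, and as written none of this would be evaluated economically.

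At stake is the figure meant to support roll-out, and whether the trial answers its own cost question whatever the primary result.

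**Working it through.** **Inputs from the protocol (Power calculation).** Missed STEMI 36% v 20%, a difference of 16 points; 280 patients (140 per arm) before clustering, at 80% power and p=0.05; 338 in total (26 × 13); stated design effect 1.24.

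**The plan's own figures.** For 36% v 20% at two-sided 0.05 and 80% power (sidedness is not stated; two-sided is assumed), the usual formula gives 246 in total without continuity correction and 270 with it, so 280 is not reproduced exactly. Cluster size 13 and ICC 0.015 give 1 + (13 − 1) × 0.015 = 1.18, not 1.24. The total of 338 lies between 280 × 1.18 = 330.4 and 280 × 1.24 = 347.2. These are separate matters; both design effects are carried below.

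**Assumptions.** Equal arms, a normal approximation, and incremental cost per patient held fixed, so that the ratio varies as 1/effect. Two readings of the condition are tried: any favourable estimate, or two-sided p<0.05 in favour.

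**Formulas.** Effective size per arm n = (338/2)/DE. With p1 = 0.36 and p2 = p1 − d:
- SE = √{[p1(1 − p1) + p2(1 − p2)]/n}
- SE0 = √{2p̄(1 − p̄)/n}, where p̄ is the mean of p1 and p2
- Threshold c = 0, or c = 1.96 × SE0
- P(pass) = Φ((d − c)/SE)
- Mean effect given pass = d + SE × φ((c − d)/SE)/P(pass)
- Median ratio relative to truth = d/(median effect given pass)

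**Worked case: DE 1.18, d = 0.16, p<0.05.**
- n = 169/1.18 = 143.2
- SE = √(0.3904/143.2) = 0.0522; SE0 = √(0.4032/143.2) = 0.0531; c = 0.104
- P(pass) = Φ(0.056/0.0522) = 0.858
- Mean effect given pass = 0.1737, and 0.1737/0.16 = 1.085
- Median effect given pass = 0.1693, and 0.16/0.1693 = 0.945

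**Results (DE 1.18 / DE 1.24).**

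| True difference | Condition | No economic result | Mean effect ÷ truth | Median ratio ÷ truth |
|---|---|---|---|---|
| 16 points | any favourable | 0.1% / 0.1% | 1.001 / 1.001 | 1.00 / 1.00 |
| 16 points | p<0.05 | 14% / 16% | 1.085 / 1.096 | 0.945 / 0.937 |
| 10 points | any favourable | 3% / 4% | 1.04 / 1.05 | 0.98 / 0.98 |
| 10 points | p<0.05 | 55% / 57% | 1.48 / 1.51 | 0.708 / 0.695 |
| 0 | any favourable | 50% / 50% | – | – |
| 0 | p<0.05 | 97.5% / 97.5% | – | – |

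A simulation of 2,000,000 draws per setting gives the same figures to within rounding. The median is used for the ratio because the inverse of the mean effect is not the typical ratio.

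**The case against.** **Assuming may express an expectation rather than a rule.** The protocol hypothesises improvement, writes in an anticipatory style elsewhere, and plans the linkage unconditionally, partly to inform cost-effectiveness. That reading is possible, but it is not the plain one. If it is what was meant, stating it costs nothing.

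**The bias may be tiny.** This stands in part. A reader might infer that the cost ratio will be badly understated. The documents do not support that at the planned effect: no significance condition is stated, and with 338 patients power is about 84% to 86%. The larger figures need both a p<0.05 condition and a true effect well below 16 points.

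**Cost is not fixed.** This stands. The protocol counts hospital stay, treatments and readmissions as costs and expects more urgent transfers as diagnosis improves, so incremental cost may move with the number identified. The percentages are illustrative; the selection on the denominator remains.

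**A null trial would still yield cost information.** This also stands. A reader might infer that the trial would then say nothing about costs. That is too strong: Expected impacts of research promises estimates of the time the central service needs, and utilisation data are linked in any case. What would be missing is a planned economic evaluation.

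**The Project summary does not contradict the economic section.** A reader might infer a direct conflict. The summary carries no explicit condition, but its wording also presupposes an increase, so the contrast is weak.

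**Conclusion.** The point holds. On its plain reading the protocol makes every economic evaluation conditional on an undefined improvement, and the estimate that opens the gate is also the denominator of the ratio. The direction of the bias is clear: the reported cost per extra STEMI identified tends to be too low. Its size depends on what improvement means and on the true effect, running from nothing of consequence to about 30% in the median ratio across the 16- and 10-point cases tabulated, with incremental cost held fixed. The gap after a null or adverse result does not depend on those percentages, and it has no justification for the cost-consequence analysis. Priority is modest, because the weakness is confined to the economic evaluation.

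**What to change.** Remove the opening condition for evaluations 1 and 2. State that the within-trial cost-effectiveness and cost-consequence analyses will be done whatever the primary result, reporting joint uncertainty in cost and effect with clustering by hospital respected. The method for doing so can be left to the analysis plan. The ten-year model may stay conditional, provided the protocol defines the improvement that triggers it.

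The change is about one sentence and leaves recruitment, randomisation and the clinical analyses as they are. The outcome and linkage data are already planned unconditionally. The protocol does not describe how intervention costs and hospital unit costs will be captured, so the change is not wholly free: the downside is some economist time if the result is null.
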